## Plans to promote participant retention and complete follow-up {18b}

To induce patients’ motivation of following their diet, the dietitian will assure them to prescribe a stabilized diet at the end of the study. Furthermore, the dietitian will be readily available to guide and advise individuals via phone, email, and other media.

## Data management {19}

### Data management and analysis

The SPSS software (version 19) will be used for data analysis. Initially, the Kolmogorov–Smirnov test will be used to check the normality of the data. Data with normal distribution will be used to compare within-group and inter-group means by Student’s *t*-test. For data that do not have a normal distribution, Wilcoxon and Mann–Whitney tests will be used for intragroup and intergroup comparisons. In addition, the chi-square test will be used to examine qualitative data. The N-IV software will be used to analyze diet data. A *P*-value less than 0.05 will be considered significant.

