#### Secondary outcomes

The secondary outcomes are including body mass index (BMI), fat body mass (FBM), lean body mass (LBM), body fat percentage, waist circumference, insulin level as well as sex hormones (testosterone, LH, FSH, DHEA), lipid profile (cholesterol, triglycerides, low-density lipoprotein (LDL), high-density lipoprotein (HDL)), glucose levels, HOMA index – IR, physical activity, health-related quality of life (SF-36), and Ferriman-Gallwey score, before and after the intervention.

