After at least 10 h of fasting, 10 ml venous blood sample will be drawn by venous puncture from the bronchial vein of the participants to assess fasting blood sugar (FBS), insulin level, sex hormones, and lipid profile. Luteinizing hormone (LH), follicle-stimulating hormone (FSH), dehydroepiandrosterone sulfate (DHEA), testosterone, and insulin levels will be evaluated by immunochemiluminescent method, blood glucose by the enzymatic method with hexokinase, total cholesterol, high-density lipoprotein (HDL), low-density lipoprotein (LDL), and triglycerides by enzymatic colorimetric assay. The hormonal status evaluation will be performed during the follicular phase of the menstrual cycle, between the first and the seventh day. The Homeostatic Model Assessment (HOMA-IR) index will be calculated according to the formula (insulinemia mU/ml × glycemia mg/dL/450). After the first evaluation, patients will undergo the intervention, until the end of 2 months when they will be re-evaluated in the same way. All biochemical tests will be assessed clinically at the Reference Laboratory of Kermanshah University of Medical Sciences.

3.Ferriman-Gallwey score

Hirsutism is considered as one of the common clinical symptoms of polycystic ovary syndrome which is due to hyperandrogenism. It is estimated that 70% of women with PCOS also manifest hirsutism symptoms. Hirsutism is evaluated by the Ferriman-Gallwey score [30, 31].

4.Quality of life questionnaire

The quality of life questionnaire for women with polycystic ovary syndrome has been validated previously and used to both determine the psychological impact of having PCOS and the effect of participation in the intervention [30, 32]. Thus, it will be used in this study with the same purpose.

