## Statistical methods

### Statistical methods for primary and secondary outcomes {20a}

Data analysis will be done using SPSS Statistics (version 19, NY, USA). A two-tailed statistical significance will be accepted at *P* < 0.05. Each outcome variable assessed will be analyzed according to diet (PLCD or KD) and time (before and after each diet) using a repeated-measures two-way analysis of variance (ANOVA). Where appropriate, a Student–Newman–Keuls post hoc test will be used to assess the origin of any significant differences detected by the ANOVA models. Variables will be adjusted for potential confounders which will be determined using multiple linear regressions.

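### The Kolmogorov–Smirnov rule for choosing tests is unreliable at about 18 per arm and conflicts with the planned ANOVA, and every route keeps possibly skewed secondary markers on the raw scale

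*Protocol article*

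**What the plan says.** Two sections of the protocol article prescribe the analysis.

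- **Data management and analysis** starts with a normality check: "Initially, the Kolmogorov–Smirnov test will be used to check the normality of the data". Student's t-test applies if the check is passed; the rule opens with "Data with normal distribution will be used to compare within-group and inter-group means by" and then names that test. If it is failed, "For data that do not have a normal distribution, Wilcoxon and Mann–Whitney tests will be used for intragroup and intergroup comparisons". The significance rule for the P-value reads "value less than 0.05 will be considered significant". The section does not say whether the check uses the Lilliefors correction, is run per arm or pooled, or is applied to single values or to changes. It names no transformation.
- **Statistical methods for primary and secondary outcomes {20a}** has this scope: "Each outcome variable assessed will be analyzed according to diet (PLCD or KD) and time (before and after each diet". The method it names is a two-factor ANOVA for repeated measures. No normality check precedes it.

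The markers at issue are secondary outcomes: "insulin level as well as sex hormones (testosterone, LH, FSH, DHEA), lipid profile", together with glucose and HOMA-IR. For the last, "The Homeostatic Model Assessment (HOMA-IR) index will be calculated according to the formula", which multiplies insulin by glucose and divides by a constant. The primary outcome is weight loss. The sample size section plans on 18 evaluable women per arm, 23 after allowance for losses.

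**The concern.** A non-significant normality test in a small sample is weak evidence of normality, yet the rule uses it to choose the analysis. Three things follow.

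1. The choice of test depends on chance and on options that the protocol leaves open. Insulin and HOMA-IR, which is built from insulin, could end up under different tests in the same report.
2. The article gives two different answers to which test is used for a given outcome.
3. None of the stated tests works on the log scale, where positive, right-skewed laboratory values with proportional changes are usually best compared.

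Insulin and androgens carry the mechanistic rationale set out in the introduction. In a trial of 46 women, an avoidable loss of power on these markers could hide a real difference between the diets.

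**Working it through.** **Inputs from the protocol.** 18 evaluable per arm, 25% loss, 23 randomised per arm (Sample size); two-sided 0.05.

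**Inputs assumed.** Log-normal values and multiplicative effects. Log-SD s = 0.4 to 0.7 corresponds to CV = √(exp(s²) − 1) = 0.42 to 0.80. The within-woman correlation is also assumed.

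**1. The plan's own figure.** 18 × 1.25 = 22.5, rounded up to 23, as stated. The 18 itself does not follow from the printed two-sided inputs. (1.960 + 0.842)² × (2.42² + 0.8²) = 7.849 × 6.4964 = 50.99. Dividing by 1.48² gives 23.3 (24 per arm), and dividing by 2² gives 12.7 (13 per arm). That is a separate matter; 18 is taken here as stated.

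**2. Which test governs.** With two time points, the diet × time F statistic equals the square of the two-sample t statistic on change. The ANOVA is therefore a t-test on raw change, whatever the normality check returns. For a variable that fails the check, one section calls for Mann–Whitney and the other for this ANOVA.

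**3. How often the check flags skew.** Chance of rejection in one arm of 18 (20,000 samples per row):

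| log-SD | Skewness | Uncorrected, asymptotic | Uncorrected, exact | Lilliefors |
|---|---|---|---|---|
| 0.4 | 1.32 | 0.3% | 0.4% | 22% |
| 0.5 | 1.75 | 0.7% | 1.2% | 31% |
| 0.6 | 2.26 | 1.5% | 2.4% | 40% |
| 0.7 | 2.89 | 3.4% | 4.8% | 50% |

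Repeat runs gave up to 51% for Lilliefors. The unstated options matter. At log-SD 0.5, Lilliefors flags 31% in one arm, 53% if either arm may trigger the switch, and 57% in a single sample of 36. The uncorrected test flags about 1%, 1% and 5%.

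**4. Split of related outcomes.** Assume insulin log-SD 0.5 to 0.7, normal glucose with mean 95 and SD 10, 18 per arm, and a switch if either arm rejects. Insulin and HOMA-IR then go to different tests in 16 to 22% of trials with Lilliefors and 3 to 6% without.

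**5. Power on one assumed scenario.** 23 × 0.75 = 17.25, so 17 per arm. Values fall to 0.85 of baseline in one arm and 0.55 in the other; log-SD 0.5 to 0.7; correlation 0.5 to 0.7.

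| Analysis | Power |
|---|---|
| t-test on raw change | 23–59% |
| Mann–Whitney on raw change | 27–63% |
| t-test on log change | 43–88% |

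Repeat runs agree to within about 2 points. At both ends of the range the rank test gains only 4 points over the raw t-test (27 − 23 and 63 − 59).

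**6. Separating the check from the scale.** 18 per arm, correlation 0.6, effect set so that the log t-test has 80% power. Power on raw change:

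| log-SD | Always Mann–Whitney | Uncorrected check | Lilliefors check |
|---|---|---|---|
| 0.5 | 58.1% | 55.0% | 57.8% |
| 0.8 | 51.8% | 43.0% | 50.9% |
| 1.0 | 48.7% | 38.6% | 48.0% |

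- Loss from the raw scale, even if Mann–Whitney were always used: 80 − 58.1 = 21.9 up to 80 − 48.7 = 31.3 points.
- Extra loss from the uncorrected check: 58.1 − 55.0 = 3.1 up to 48.7 − 38.6 = 10.1 points.
- Extra loss from the Lilliefors check: 0.3 to 0.9 points.
- On end values instead of changes, the whole loss against the log t-test is 80 − 75.3 = 4.7 to 80 − 70.6 = 9.4 points (uncorrected) or 80 − 77.8 = 2.2 to 80 − 77.3 = 2.7 points (Lilliefors).

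**7. False positives.** Type I error of the two-stage procedure stayed between 4.4% and 5.7%.

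**The case against.** The strongest reply is that the methods section, not the data management section, fixes the main analysis. On that view the normality check concerns only supporting comparisons, and transformations belong in an analysis plan that is not shown. Part of this stands: a reader who infers that the check decides the test for every outcome overlooks the ANOVA. But the article does not rank the two sections, both cover between-diet comparisons, and the ANOVA is itself a raw-change test. The conflict is on the page and is not a detail left out.

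Two stronger readings are tempting and are not supported.

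- **That the check cannot detect skew at this size.** This is nearly true of the uncorrected test only. With Lilliefors, detection is partial, and the protocol does not say which version will be used.
- **That the check causes a large loss of power.** Even a check that always chose the rank test would leave most of the gap. The cause is the raw change scale. On end values the loss is small under either version.

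It is also fair to say that the simulation favours logs by design, since it generates log-normal data with multiplicative effects. The documents give no SD, skewness or correlation for any of these markers, so the power figures illustrate the risk and do not predict this trial's results.

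**Conclusion.** The concern holds as a minor point. The test-selection rule is unreliable at the planned size and contradicts the ANOVA assigned to every outcome. These two findings rest on the text and on the behaviour of the test in small skewed samples. The power cost is conditional: it arises if the markers are right-skewed with proportional effects and are analysed as changes, and then it comes mainly from the raw scale. A reader might also infer inflated false positives or damage to the primary outcome. Neither is shown, since type I error is not materially affected and the markers concerned are all secondary outcomes.

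**What to change.** - Delete the normality check, and merge the two sections into one prespecified between-diet model for each outcome, for example end value on diet with adjustment for baseline.
- List in advance the markers to be analysed on the log scale: insulin, glucose, HOMA-IR, triglycerides, and the hormones expected to be skewed (for example testosterone, LH and DHEA). Report ratios of geometric means with 95% confidence intervals. Glucose belongs on the list because log HOMA-IR is then log insulin plus log glucose minus a constant, so all three share one scale.
- Keep Wilcoxon and Mann–Whitney tests as sensitivity analyses only.

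The cost is a change of wording with no new data or visits. The small downside is that these markers are reported as percent and not unit differences. Because the documents give no distributions, the list is a judgement and should be fixed before outcome data are seen.

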### Sample size {14}

According to the formula, the standard deviation of weight in the dietary group of PLCD and KD would be equal to μ_1_ = 3.14 (σ_1_ = 2.42) and μ_2_ = 1.66 (σ_2_ = 0.8) respectively. In the following sample with *α* = 0.05, the sample size required to have 80% power to detect a difference of 2 units of change in weights would be 18 people in each group. Considering the possibility of 25% missing people in the follow-up, the sample size increases to 23 people in each group.$$n=\frac{{\left({z}_{1-\frac{a}{2}}+{z}_{1-\beta }\right)}^{2}+\left({\sigma }_{2}^{1}+{\sigma }_{2}^{2}\right)}{{\left({\mu }_{1}-{\mu }_{2}\right)}^{2}}$$

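### The plan sizes the trial on a nine-fold variance ratio but fixes pooled-variance tests, so the 5% level drifts modestly when the analysed arms are unequal

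*Protocol article*

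**What the plan says.** - **Sample size {14}.** The planning values for PLCD and KD "would be equal to μ_1_ = 3.14 (σ_1_ = 2.42) and μ_2_ = 1.66 (σ_2_ = 0.8) respectively". The printed formula carries a separate variance for each arm. The result is given as "80% power to detect a difference of 2 units of change in weights would be 18 people in each group", and then "Considering the possibility of 25% missing people in the follow-up, the sample size increases to 23 people in each group".
- **Data management and analysis (under {19}).** For normally distributed data the plan will "compare within-group and inter-group means by Student’s *t*-test". Wilcoxon and Mann–Whitney tests replace it when normality fails.
- **Statistical methods {20a}.** Each outcome "will be analyzed according to diet (PLCD or KD) and time (before and after each diet) using a repeated-measures two-way analysis of variance (ANOVA". Testing is two-sided: "A two-tailed statistical significance will be accepted at *P* < 0.05". Adjustment for confounders by linear regression is also mentioned.
- **Missing data {20c}.** Analysis is by intention to treat. Multiple imputation is planned if more than 10% of the primary outcome is missing. The imputation model is not described.

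None of these sections names an unequal-variance test, arm-specific variances or robust standard errors.

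**The concern.** The plan expects the spread of weight change to be three times as large on PLCD as on KD, yet both named tests estimate one common variance. With equal arms this hardly matters. With unequal arms, the pooled variance is weighted towards the larger arm, and the standard error of the difference is then wrong. If PLCD (the more variable arm) ends up smaller, the standard error is too small and the test rejects too often. If KD ends up smaller, the test is too strict and loses power.

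Weight loss is the single primary outcome and about 35 women are expected to provide data, so a modest imbalance is enough to move the P-value and the confidence interval.

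**Working it through.** **Inputs.** From Sample size {14}: σ₁ = 2.42 (PLCD), σ₂ = 0.8 (KD), means 3.14 and 1.66 (difference 1.48), 23 women per arm, 25% loss. From {20a}: two-sided 5%. I read the means and SDs as those of weight change, because the same section speaks of a difference in change.

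**The plan's own figure.** With the usual formula n = (z₁₋α/₂ + z₁₋β)²(σ₁² + σ₂²)/δ², two-sided 5% and 80% power:
- δ = 1.48: 7.849 × 6.496 / 2.190 = 23.3, so 24 per group.
- δ = 2: 7.849 × 6.496 / 4 = 12.7, so 13 per group.

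Neither gives the stated 18. That is a separate fault. It matters here only because the formula uses two unequal variances.

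**Variance ratio.** 2.42² / 0.8² = 5.856 / 0.64 = 9.15.

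**Why the two named tests share the problem.** With one measurement before and one after, the diet-by-time F in the repeated-measures ANOVA equals the square of the pooled two-sample t on change scores.

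**Direction of the error.** Compare the variance of the difference that pooling targets with the true one:
- Pooled: [((n₁−1)σ₁² + (n₂−1)σ₂²)/(n₁+n₂−2)] × (1/n₁ + 1/n₂)
- True: σ₁²/n₁ + σ₂²/n₂

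| PLCD/KD | Pooled | True | Ratio |
|---|---|---|---|
| 19/23 | 2.987 × 0.0961 = 0.287 | 0.308 + 0.028 = 0.336 | 0.85 |
| 23/19 | 3.509 × 0.0961 = 0.337 | 0.255 + 0.034 = 0.288 | 1.17 |
| equal arms | – | – | 1.00 |

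**True two-sided level at nominal 5%.** Simulated normal data with the SDs above, complete cases:

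| PLCD/KD analysed | Pooled t or ANOVA | Welch |
|---|---|---|
| 23/23 | 5.4% | 5.0% |
| 18/18 | 5.5% | 5.0% |
| 17/18 | 6.1% | 5.0% |
| 16/19 | 7.3% | 5.0% |
| 19/16 | 4.0% | 5.0% |
| 19/23 | 7.4% | 5.0% |
| 23/19 | 3.8% | 5.0% |
| 14/21 | 10.2% | 5.0% |
| 13/22 | 12.0% | 5.1% |
| 21/14 | 2.5% | 5.0% |

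Power for a difference of 1.48 is 67% (pooled) against 65% (Welch) at 18/18, and 58% against 71% at 21/14.

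**How likely is imbalance?** If each woman independently has a 25% chance of loss, the arms finish exactly equal in about 14% of trials and differ by three or more in 39%. If exactly 11 of 46 are lost at random, the average true level over all splits is about 5.7%. In that case PLCD falls to 14 or fewer with probability 1.8%, and to 13 or fewer with probability 0.2%.

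**Effect of the imputation rule.** Four of 46 missing is 8.7%, below the trigger; five is 10.9%, above it. So up to four losses are analysed without imputation, and the worst cases are the 19/23 and 23/19 rows. Above the trigger, imputing back to 23/23 and then using the pooled test gives:

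| Observed PLCD/KD | Common residual variance | Separately by arm |
|---|---|---|
| 17/23 | 8.5% | 5.0% |
| 23/17 | 2.8% | 5.1% |
| 14/22 | 10.4% | 5.0% |
| 22/14 | 1.9% | 5.0% |

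**The case against.** The strongest objection is the imputation rule in {20c}. With the planned loss, about 35 of 46 women have data. That is 24% missing, so imputation is triggered and the analysed arms are 23/23 rather than 14/21. This stands in part. The 10–12% and 2.5% figures are complete-case results, and imputation by arm removes the error. Imputation with a common residual variance does not, and the article does not say which is meant. Leaving the imputation model to a fuller document is normal and is not the fault here; the point is that the rule does not by itself cure the problem.

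Second, the extreme splits are tail cases. The article assumes one loss rate for both arms and nowhere predicts more loss on PLCD. The short-term complications in {11b} and {22} are listed for KD. This stands in full, and it limits the size of the finding.

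Third, the SDs come from a section with faults of its own, and their source is not described. True, but they are the plan's only statement about spread. If they are wrong and the variances are in fact similar, an unequal-variance test costs little.

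Fourth, Student's t-test may be a loose label, and software may also print an unequal-variance result. The plan does not commit to that result, and the ANOVA it also names pools the variances. The Mann–Whitney fallback is triggered by non-normality, not by unequal spread.

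**Conclusion.** The point holds as a modest and easily avoided mismatch between the planning assumption and the named tests. If the stated SDs are right and the data are normal, the true level is about 5.4–5.5% with equal arms and averages about 5.7% under random loss of 11 women with complete cases analysed. It runs from about 4% to about 7.4% at the small imbalances that are realistic, including those below the imputation trigger.

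A reader might infer that the primary test will run at 10–12%, or that its P-value is bound to be wrong under the plan's own assumptions. The documents do not support that. Those levels need marked differential loss that the article does not predict, together with complete-case analysis or common-variance imputation. The splits shown are assumptions of this check.

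**What to change.** For weight change and the other continuous outcomes, replace the pooled-variance comparison with one of these:
- Welch's t-test on change; or
- a linear model with heteroscedasticity-robust (HC3) or arm-specific variances, which also allows the planned adjustment.

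Take the 95% confidence interval from the same model. State that any multiple imputation under {20c} is done separately by arm. This is needed as well as the change of test: once the arms are filled back to 23/23, the Welch and pooled standard errors coincide, so Welch alone cannot undo a common-variance imputation.

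The cost is a sentence or two of text and 1–2 points of nominal power at exactly equal arms (65% against 67% at 18/18). Part of that difference reflects the pooled test running slightly above 5%. No change to recruitment or data collection is needed.

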### Confidentiality {27}

The data of all of the participants will be kept in Kermanshah university and just investigators of this trial will have access to them**.**

### Plans for collection, laboratory evaluation, and storage of biological specimens for genetic or molecular analysis in this trial/future use {33}

At the beginning and end of the intervention, 10 cc of venous blood will take from all patients in the fasting state and in the early follicular phase (days 3–8 of the menstrual cycle), and after centrifugation, the plasma will be stored at – 80 °C until hormonal and biochemical tests. Sampling and specialized tests are carried out in the central laboratory of the Kermanshah University of Medical Sciences under the supervision of physicians and relevant experts.

## Statistical methods

### Statistical methods for primary and secondary outcomes {20a}

Data analysis will be done using SPSS Statistics (version 19, NY, USA). A two-tailed statistical significance will be accepted at *P* < 0.05. Each outcome variable assessed will be analyzed according to diet (PLCD or KD) and time (before and after each diet) using a repeated-measures two-way analysis of variance (ANOVA). Where appropriate, a Student–Newman–Keuls post hoc test will be used to assess the origin of any significant differences detected by the ANOVA models. Variables will be adjusted for potential confounders which will be determined using multiple linear regressions.

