### Outcomes {12}

#### Primary outcomes

The primary outcome of this investigation is to determine the effectiveness of the PLCD compared to the KD in improving PCOS disease symptoms by measuring weight loss before and after the intervention.

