### Methods in analysis to handle protocol non-adherence and any statistical methods to handle missing data {20c}

An “intention to treat” analysis will be conducted to handle protocol non-adherence. In the case of more than 10% missing for the primary outcome, we plan to impute missing values using the multiple imputation method.

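### Two unreconciled analyses cover the primary outcome, and neither names the between-diet contrast in weight change as the primary test

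*Protocol article*

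**What the plan says.** The primary outcome compares the diets "in improving PCOS disease symptoms by measuring weight loss before and after the intervention" (Protocol article, Primary outcomes). Two sections then say how outcomes will be tested.

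- **Data management and analysis {19}.** A Kolmogorov-Smirnov result decides the method. If normality is accepted, Student t serves both kinds of comparison; the sentence begins "Data with normal distribution will be used to compare within-group and inter-group means by" and then names that test. If it is rejected, rank tests take over: Wilcoxon inside each arm, Mann-Whitney across arms.
- **Statistical methods for primary and secondary outcomes {20a}.** Each outcome is "analyzed according to diet (PLCD or KD) and time (before and after each diet) using a repeated-measures two-way analysis of variance (ANOVA". Newman-Keuls comparisons are to locate the source of a significant ANOVA result. On covariates the section ends: "Variables will be adjusted for potential confounders which will be determined using multiple linear regressions".

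The section on additional analyses {20b} adds adjustment for waist circumference, macronutrient intake and physical activity. The sample-size section {14} plans on a between-group difference in weight change. On missing data, {20c} says: "In the case of more than 10% missing for the primary outcome, we plan to impute missing values".

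**The concern.** Both sections apply to weight, neither refers to the other, and no rule says which prevails. This is more than detail left to an analysis plan: the article makes two positive statements that can give different p-values for the primary outcome.

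The treatment contrast is also left open. The ANOVA is described by its two factors, diet and time, but the diet-by-time term is not named. The t-test and Mann-Whitney wording does not say whether change or week-8 values are compared. An analyst following the text could report the diet main effect, the interaction, a t-test on change, a t-test on end values, a rank test or a covariate-adjusted version. If that choice is made after the data are seen, type I error is not controlled. If the wrong term is read as the answer, the trial has almost no power.

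Two diets at two times leave nothing for Newman-Keuls to do unless all four diet-by-time cells are compared, and that is not the randomised comparison. The within-group tests likewise invite a conclusion from significance in one arm only.

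**Working it through.** **Inputs from the sample-size section.** PLCD 3.14 (SD 2.42), KD 1.66 (SD 0.8), read here as mean and SD of weight change; two-sided alpha 0.05; 23 per arm. The difference of means is 3.14 − 1.66 = 1.48. **Assumed, not in the documents:** between-woman SD of body weight 8 to 15 kg, normal data, change independent of baseline.

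**The plan's own figure.** The usual formula is n = (1.96 + 0.842)² × (2.42² + 0.8²) / δ², with numerator 7.849 × 6.496 = 50.99.
- δ = 2: 50.99 / 4 = 12.7, so 13 per arm.
- δ = 1.48: 50.99 / 2.190 = 23.3, so 24 per arm.

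The stated 18 per group is not reproduced. That is a separate matter; what follows uses only the means, the SDs and 23 per arm.

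**Which term is the treatment effect.** Let d be the between-arm difference in mean change, s² the pooled variance of change and n the number per arm. With two arms and two times:
- interaction sum of squares = n d² / 4
- within-woman error mean square = s² / 2
- F = n d² / (2 s²) = d² / (2 s² / n) = t²

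One simulated data set gave 10.2736 for both F and t². So the ANOVA interaction and Student t on change are the same test.

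**Power by choice of term (true difference in change 1.48, 23 per arm).**
- Change or interaction: SE = √(6.496 / 23) = 0.531; 1.48 / 0.531 = 2.78; power about 78%.
- Diet main effect (average of baseline and end): the expected difference is 1.48 / 2 = 0.74. At SD 12, SE = √[(2 × 144 + 6.496 / 4) / 23] = 3.55, ratio 0.21, power about 5.5%. Across SD 8 to 15, 5-6%.
- End values: at SD 12, SE = √[(2 × 144 + 6.496) / 23] = 3.58, ratio 0.41, power about 7%. Across SD 8 to 15, 6-9%.

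**Type I error when analyses compete (simulation, no true difference, SDs 2.42 and 0.8, 23 per arm).**

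| What may be reported | Rejection rate |
|---|---|
| Student t on change only | about 5.5% |
| Better of t and Mann-Whitney on change | about 8% |
| Better of interaction and diet main effect | about 10% |
| Best of these and the end-value test | about 13% |

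With equal SDs of 1.8, the better of t and Mann-Whitney gives about 6%, and the better of interaction and main effect about 10%. The main-effect inflation therefore does not come from the unequal variances.

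**Within-group tests.** If both diets truly produced the same mean loss of 1 unit (assumed), exactly one arm would be significant on its own in about 53% of trials, because the SDs differ.

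**Equal variance.** The variance ratio is 5.856 / 0.64 = 9.2. At 23/23 Student t rejects about 5.4% and Welch 5.0%. At 19 PLCD and 23 KD completers Student t gives 7.4% against 5.0% for Welch; at 23/19 it gives 3.8%.

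**The case against.** The strongest reply is that the sections conflict less than they seem to. Student t on change and the ANOVA interaction are one test, and both the primary outcome and the sample-size section point to change. The 5-6% power applies only to someone who reads the wrong term. This stands in part: a reader might infer that neither analysis isolates the diet effect, and that is not so. Both contain the right contrast; the fault is that neither names it. The rank branch, the main effect, end values and adjusted versions remain open and do give different answers.

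A reader might also infer that unequal variances seriously distort the planned test, since completer-only Student t gives 8.7% at 15 PLCD and 20 KD, and 12% at 13/22. The documents do not support that as the expected case. Those splits leave 35 of 46 women, 24% missing, where {20c} calls for multiple imputation. Imputing within arm gave about 4.4% at both splits; imputing with one pooled variance gave 8.7% and 11.4%. The result thus turns on a detail commonly left to an analysis plan. With up to 4 of 46 missing, where imputation is not triggered, the worst case is the 7.4% above. Nor does the criticism extend to the Mann-Whitney branch as a pooled-variance test, although that branch is not exact here either (6.7% at 23/23).

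Two further readings go too far. The phrase about before and after each diet might suggest a crossover, but the trial design and study setting sections say parallel-arm. And {20c} is silent at or below 10% missing; it does not say that only completers are then analysed.

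**Conclusion.** The point holds: two analyses of the primary outcome are prescribed without a rule between them, and the primary contrast is not named. This should be corrected before analysis, because the primary test cannot be identified from the document. The possible choices run from about 78% power to 5-9%, and post hoc choice raises type I error from about 5% to between 8% and 13%.

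The power figures rest on the plan's own means and SDs and on an assumed body-weight SD of 8 to 15 kg. The type I error figures also assume that the most favourable result is the one reported; the documents do not say that this is intended. Unequal variance is a secondary point: nearly harmless at 23/23, and of consequence only if completers are unbalanced.

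**What to change.** State one primary analysis, in the same words, in {19} and {20a}:

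- the between-diet difference in week-8 weight adjusted for baseline weight, or in weight change, in all randomised women;
- unequal-variance standard errors (Welch on change, or a linear model with robust errors) and a 95% CI;
- this comparison as the only confirmatory test.

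Use the same model for the secondary outcomes, log-transforming skewed hormones. Delete the Kolmogorov-Smirnov gate, Newman-Keuls and the within-group p-values. Take the regression-selected confounders in {20a} out of the primary test, and likewise the adjustment in {20b} for macronutrient intake and physical activity. Intake during the trial is what the diets are meant to change, so adjusting for it would remove part of the effect.

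The cost is wording in these sections, a little programming and a small loss of power when arms stay balanced. Welch on change costs about 1 point at 23 per arm (about 78% to 76.5%). A baseline-adjusted model with HC3 errors, one robust option, costs about 2 points at 23 per arm (76% to 74%) and 4 at 18 per arm (66% to 62%).
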